## Abstract

**Background:** Flexor spasticity of the upper limb is common in poststroke patients and seriously affects the recovery of upper limb function. However, there are no standard management protocols for this condition. Radial extracorporeal shock wave therapy (rESWT) is widely used for various diseases, some studies reported the effects of ESWT on reducing spasticity, but the mechanism of ESWT to reduce spasticity by affecting the excitability of stretch reflex or non-neural rheological components in spastic muscles or both is not yet clear. A large randomized controlled trial with comprehensive evaluation indicators is still needed. The study is to observe the effect of rESWT on flexor spasticity of the upper limb after stroke and explore its mechanism.

**Methods:** A prospective, randomized, double-blind controlled trial is to be performed. One hundred participants will be recruited from the Inpatient Department of Zhujiang Hospital. Eligible patients will be randomly allocated to either receive three sessions of active rESWT (group A) or sham-placebo rESWT (group B) with 3-day intervals between each session. Assessment will be performed at baseline and at 24 h after each rESWT (t1, t2, and t3). The primary assessment outcome will be the Modified Ashworth Scale, and other assessments include surface electromyography, MyotonPRO digital muscle function evaluation, and infrared thermal imaging. All data will be analyzed using intention-to-treat principles. Multiple imputation by chained equations will be used to address missing data caused by loss to follow-up and nonresponses. Per protocol, analyses will also be performed on the participants who complete other assessments. Statistical analysis will be performed using SPSS software (version 20.0) and the significance level set at *p* < 0.05.

**Discussion:** This trial aims to analyze the application of rESWT for the management of spasticity after stroke *via* appropriate assessments. We hypothesized that after receiving active rESWT, patients would show greater improvement of upper limb muscles compared with patients within the sham-placebo group. The rESWT would be an alternative to traditional methods, and the results of this study may provide support for the further study of potential mechanisms.

**Clinical Trial Registration:**www.chictr.org.cn, identifier: ChiCTR1800016144.

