### Participants

Patients with flexor spasticity of the upper limb after stroke (Table 2).

**Table 2 T2:** Flow chart of the study.

**Items/Time points**	**Enrollment**	**Allocation**	**Post-allocation**		
	***-t1***	**Baseline**	***t1***	***t2***	***t3***
Basic medical history	×				
Eligibility screen	×				
Informed consent	×				
Allocation(Group A/Group B)		×			
Intervention(Group A/Group B)		×			
Assessments	MAS		×	×	×	×
	H reflex		×			×
	MCV		×			×
	RMS		×	×	×	×
	iEMG		×	×	×	×
	CR		×	×	×	×
	MyotonPRO		×	×	×	×
	IRT		×	×	×	×

*Group A, active rESWT; Group B, sham-placebo rESWT; MAS, Modified Ashworth Scale; MCV, Motor nerve conduction velocity; RMS, Root mean square value; iEMG, Integrated electromyogram; CR, co-contraction ratio; IRT, Infrared Thermal Imaging; t1/ t2/ t3, at 24 hours after the first/ second/ third radial extracorporeal shock wave therapy*.

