### Sample Size Calculation

The known effectiveness of poststroke spasticity treatment using conventional methods is 64.5%, whereas preliminary experiments with ESWT have shown expected effectiveness of 80%, with two-tailed tests of a significance level of α = 0.05 and β = 0.1, which is expected to fall off at a rate of 10%, using professional software Advisor nQuery sample size estimation, for a sample size of 45 cases in each group, which can be considered as a loss rate of approximately 10%. Therefore, for this study, a sample size of 50 cases in each group was decided on, with a total sample size of 100 cases.

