### Statistical Methods

The primary comparisons for MAS will be made using repeated measures mixed-effect model with terms of treatment, time, and corresponding baseline values as covariates. We will first examine the intervention by time interaction and then proceed to the main effects model with only group and time.

Repeated analysis of variance with *post-hoc* test will be used to compare changes between active rESWT intervention and sham rESWT intervention groups from baseline to the end of follow-up when data are normally distributed, and the Mann–Whitney U-test will be used when data are not normally distributed. A chi-square test will be used for dichotomous variables.

In secondary analyses, repeated measures mixed model will also be used to examine the associations between treatments and repeated measures outcomes. Additionally, linear regression and/or logistic regression analyses will be used to assess the associations between treatments and changes or increases in outcomes from baseline to the end of follow-up in univariate and multivariate modeling adjusted for relevant covariates.

All data will be analyzed using intention-to-treat principles. Multiple imputation by chained equations will be used to address missing data caused by loss to follow-up and non-responses. Per protocol analyses will also be performed in the participants who complete other assessments, including Hmax/Mmax, MCV, RMS, iEMG, CR, MyotonPRO, and IRT. Statistical analysis will be performed using SPSS software (version 20.0) and the significance level set at *p* < 0.05.

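### The primary MAS model is inconsistent on baseline adjustment: it is defined with baseline MAS as a covariate but ends with group and time only, and no single primary MAS contrast is fixed

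*Protocol article*

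**What the plan says.** The Abstract fixes the outcome: "The primary assessment outcome will be the Modified Ashworth Scale". Table 2, under Participants, schedules MAS at baseline and at three later visits, which its footnote defines as "t1/ t2/ t3, at 24 hours after the first/ second/ third radial extracorporeal shock wave therapy".

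Under Statistical Methods, the primary MAS comparison uses a "repeated measures mixed-effect model with terms of treatment, time, and corresponding baseline values as covariates". The next sentence reads "We will first examine the intervention by time interaction and then proceed to the main effects model with only group and time". No condition is attached to that step.

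The paragraph after it adds a between-group comparison of change by repeated analysis of variance, "from baseline to the end of follow-up when data are normally distributed", or by the Mann–Whitney U-test otherwise. It does not say how this ranks against the mixed model.

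**The concern.** The two adjoining sentences describe different final models for the primary outcome. In the first, baseline MAS is a covariate. In the second, the word that limits the model to group and time leaves no place for it. Two analysts could follow the same text and obtain different standard errors and p-values for the main result.

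The target is also left open. A main-effects model has one group term, which averages the group difference over the visits in the model. Here those visits follow one, two and three sessions. The later paragraph describes a comparison to the end of follow-up, which answers another question. Nothing says which result decides the trial.

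At stake are precision that costs nothing to keep, since baseline MAS is collected anyway, and a clear statement of what the primary result estimates.

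**Working it through.** The plan states no figure for this model, and its sample size is argued from response rates, so there is no figure of its own to reproduce here. The calculation below shows what each reading would mean.

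**Inputs from the protocol**
- Visits t1, t2 and t3 follow one, two and three sessions (Table 2).
- 50 per arm with 10% loss gives 50 × 0.9 = 45 per arm (Sample Size Calculation).
- Two-sided α of 0.05 (Sample Size Calculation).

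**Assumptions, none given in the protocol**
- MAS values are treated as continuous, with SD 1 at each visit.
- The correlation ρ is equal between all visits: 0.6, with 0.5 and 0.7 as a range.
- The effect at t3 is 0.5 SD. The profile over t1, t2, t3 is either flat (1, 1, 1) or linear (1/3, 2/3, 1), as multiples of the t3 effect.

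**Step 1: what the group main effect estimates**
- Flat: (1 + 1 + 1)/3 = 100% of the t3 effect, or 0.5 SD.
- Linear: (1/3 + 2/3 + 1)/3 = 67% of the t3 effect, or 0.333 SD.

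**Step 2: per-patient variance, in SD²**
- Average of t1 to t3 without baseline: (1 + 2ρ)/3 = 2.2/3 = 0.733.
- Average of t1 to t3 with baseline: 0.733 − ρ² = 0.733 − 0.36 = 0.373.
- t3 alone with baseline: 1 − ρ² = 0.64.

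Omitting baseline multiplies the variance of the averaged effect by 0.733/0.373 = 1.96. A patient random effect does not recover this, because group is a between-patient factor.

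**Step 3: power** = Φ(effect/√(2 × variance/45) − 1.96)

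| Final analysis, ρ = 0.6 | Standard error | Linear growth to 0.5 SD | Flat at 0.5 SD |
|---|---|---|---|
| Average, group and time only | 0.181 | 0.333/0.181 → 45% | 0.5/0.181 → 79% |
| Average, baseline kept | 0.129 | 0.333/0.129 → 73% | 0.5/0.129 → 97% |
| t3 contrast, baseline kept | 0.169 | 0.5/0.169 → 84% | 0.5/0.169 → 84% |

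**Step 4: range over ρ, averaged effect without and with baseline**

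| ρ | Variance without / with | Linear, without / with | Flat, without / with | t3 with baseline |
|---|---|---|---|---|
| 0.5 | 0.667 / 0.417 | 49% / 69% | 83% / 96% | 78% |
| 0.7 | 0.800 / 0.310 | 42% / 81% | 76% / 99% | 91% |

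Keeping baseline helps under both profiles. Between the average and t3, with baseline kept in both, the order depends on the profile. At ρ = 0.6 the average has less power only when the mean effect is below √(0.373/0.64) = 76% of the t3 effect.

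**The case against.** The strongest reply is that the second sentence contrasts a step with the interaction and a step without it. Its limit to group and time may then mean only that the interaction is removed, with baseline carried over from the sentence before. That reading is possible, and a condensed article may simply be loosely worded. It stands as a reason to call this an inconsistency to be resolved, not a proven omission. The 45% and 79% figures apply only on the literal reading.

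Three stronger inferences are tempting, and the protocol does not support them:

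- **That the end-of-treatment effect is certainly diluted.** This needs benefit to build up over sessions, and no MAS time profile is given. The Discussion points both ways: it cites a single-session study with muscle changes at every follow-up from 30 minutes, and it lists having only three sessions as a limitation. With a flat effect and baseline kept, the average does better than t3 (97% against 84%). Nor does leaving out baseline shrink the effect; it only widens the standard error.
- **That the interaction test is a data-driven first stage.** The text goes on to main effects without condition, so the interaction p-value selects nothing.
- **That baseline is counted as a fourth outcome visit.** The sentence defining the primary model makes it a covariate.

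It is also fair to say that a time-averaged effect is a legitimate target and that no sentence makes t3 the primary visit. Choosing t3 is therefore a trade-off, not a correction. Details such as the covariance structure belong in an analysis plan and are not at issue.

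**Conclusion.** The point holds as an inconsistency in the stated primary model, with an unranked set of MAS comparisons beside it. On the literal reading, the final model gives up baseline MAS. The comparison stays unbiased in expectation, but the variance of the averaged effect roughly doubles at ρ = 0.6 (1.6 times at 0.5, 2.6 times at 0.7).

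These sizes rest on an assumed SD, correlation, effect size and time profile. Eligibility requires an elbow MAS grade above 1, which narrows the baseline range and could lower the correlation. At ρ = 0.3, for example, the variances would be 1.6/3 = 0.533 and 0.533 − 0.09 = 0.443, a ratio of 1.2. The direction does not change: under these assumptions, keeping baseline gains precision at any positive correlation.

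Whether averaging over t1 to t3 helps or harms depends on the unknown profile, so what needs settling is which contrast is primary. Severity is moderate.

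**What to change.** Replace the sentence on the main-effects model with text that does three things:

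1. States that baseline MAS stays in the final primary model.
2. Names one primary MAS contrast in advance: either the group difference at t3, with group-by-time kept in the model whatever its p-value, or the group difference averaged over t1 to t3. The other is reported as supportive.
3. States that the repeated analysis of variance or Mann–Whitney comparison of change to the end of follow-up is supportive.

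The choice in item 2 is the investigators' to make on clinical grounds. A t3 contrast is the safer choice if benefit is expected to build up, and the average is the more powerful one if benefit appears early and holds.

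The cost is a wording change, made before unblinding. No added visits or measurements are needed, since MAS is already scheduled at all four time points. Trial Status reports 50 of the planned 100 patients recruited at submission.

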#### Secondary Outcome Measures

Electromyography (EMG), surface electromyography (sEMG), MyotonPRO digital muscle function evaluation system, and infrared thermal imaging (IRT) are to be used for the evaluation.

**H reflex:** H reflex of the median nerve is to be detected using the Schwarzer topas EMG system (Natus Medical Incorporated, Pleasanton, CA, USA). The recording must be conducted from the flexor carpi radialis as follows: the recording electrode is to be placed at the mid-upper 1/3 junction of the medial humeral epicondyle and the radial styloid process line, the reference electrode is to be placed at the tendon, the ground electrode is to be placed at the olecranon, and the stimulation electrode is to be placed at the median nerve proximally to the elbow. The maximal amplitude of H-reflex (H-max) and M-response (M-max) are to be recorded. The H-max/M-max value, which can reflect the excitability change of the α-motor neuron, is to be calculated to detect changes in response to the effect of rESWT on the spasmodic muscle.**Motor Nerve Conduction Velocity:** The same apparatus is to be used, but the electrodes are to be placed differently. The recording electrodes must be placed on the abductor pollicis brevis muscle belly, and the stimulating electrode must be placed on the median nerve at wrist and elbow level to record distal motor latency, MCV, and amplitude. This assessment is aimed at determining whether rESWT causes nerve injury and evaluating its safety.**Root-Mean-Square Value:** An sEMG recording is to be obtained using bipolar Ag/AgCl surface electrodes (MyoMove, Northam Electric Co., Ltd., Shanghai, China) for the sEMG assessment. The patient is to be treated while in a sitting position. The electrodes are to be placed on the fullest part of the upper limbs muscle belly. The locations at which the stimulating and recording electrodes are to be placed must be rubbed with 70% alcohol to reduce skin impedance. Electrode placement is to be done as recommended by Surface EMG Non-invasive Muscle Assessment and the International Society of Electrophysiology and Kinesiology. With the upper limbs of a patient comfortably placed on the treatment table, the resting sEMG activity of the musculus biceps brachii (BM) and flexor carpi radialis are to be measured under stable and static conditions for 30 s at a time. Also, the RMS of biceps brachii and flexor carpi radialis is calculated. RMS can be used to objectively and quantitatively evaluate the condition of muscle spasms, with a higher value indicating a more severe muscle spasm.**Integrated Electromyogram and Co-contraction Ratio:** The patient is seated with the upper body fixed to the seat with a wide nylon strap. The elbow of the patient is at a 45° flexed position and wrist in a neutral position, and the hand holds the handle of the arm strength test joystick of Biodex System 3® dynamometer (Biodex Medical Systems, Shirley, NY, USA). The electrodes are to be placed on the muscle belly of BM and musculus triceps brachii (TM). Training is to be performed for 1 min before the assessment to help patients familiarize themselves with the process. During the test, the patients are to be asked to stretch the elbow joint with maximum strength for 10 s to measure maximum isometric voluntary contraction (MIVC) of TM (44). The iEMG and CR of BM and TM are to be recorded for 20 and 5 s before and after contraction, respectively, as the basic control. The test is to be carried out three times, with an interval of 5 min between each application, and the maximum value is to be recorded. The assessment includes the iEMG of the BM and TM when the elbow is stretched for MIVC, and then the CR is calculated. The iEMG value can reflect the total amount of muscle discharge per unit time and is mainly used to analyze the contraction characteristics of muscles per unit time. CR refers to the proportion of antagonist muscles during the process of active muscle contraction (34), although it is well known that increased synergistic contraction of antagonistic muscles is a common phenomenon in stroke patients. The decrease of CR within MIVC of the elbow indicates a reduction in the strength of the biceps tendon.

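### Baseline adjustment is named only for MAS; the stated rule for other continuous outcomes tests unadjusted change, which costs precision, most clearly for H-max/M-max and MCV

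*Protocol article*

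**What the plan says.** The Statistical Methods section of the protocol article lists analyses in three layers.

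1. MAS, the primary outcome, gets a repeated-measures mixed model with treatment, time and the baseline value as a covariate.
2. Repeated ANOVA with post-hoc tests "will be used to compare changes between active rESWT intervention and sham rESWT intervention groups from baseline to the end of follow-up" if the data are normal; "the Mann–Whitney U-test will be used when data are not normally distributed". No outcome is named and no covariate is given.
3. For secondary analyses, a repeated-measures mixed model is to be used as well. In addition there are linear and/or logistic regressions of change from baseline, both univariate and adjusted for covariates called relevant but not listed.

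Nothing in layers 2 or 3 names baseline as a covariate, and nothing says which analysis decides the result for a given outcome.

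Table 2 schedules RMS, iEMG, CR, MyotonPRO and IRT at baseline, t1, t2 and t3, but the H reflex and MCV only at baseline and t3. Under Secondary Outcome Measures, the article gives the role of the H-reflex ratio: "The H-max/M-max value, which can reflect the excitability change of the α-motor neuron". MCV is there to detect nerve injury.

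**The concern.** MAS already has its own model, so the ANOVA/Mann–Whitney rule reads most naturally as the rule for the other continuous outcomes. If it is applied as written, each is judged on raw change. A change score fixes the slope on baseline at 1, whereas ANCOVA estimates it. Under randomisation both are unbiased, but ANCOVA is more precise whenever the baseline-to-follow-up correlation is below 1.

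The Abstract and Discussion say that the trial is meant to help separate neural from peripheral mechanisms. H-max/M-max is its direct measure of motor neuron excitability and has a single post-treatment value. A non-significant result from a needlessly imprecise test could be misread as evidence against a neural effect.

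Two further features of the rule are awkward. Choosing the test after a normality check leaves the analysis open until the data are seen. A Mann–Whitney test also gives no baseline-adjusted effect estimate, and it has no standard pooled result across the multiply imputed data sets planned in the same section.

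**Working it through.** **Inputs from the article.** Two-sided α = 0.05; 50 randomised per arm; 10% loss, so 50 × 0.9 = 45 evaluable per arm; H-max/M-max and MCV at baseline and t3 only.

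**Assumed, because the article does not give them.** The baseline-to-t3 correlation ρ (0.3 to 0.9); an effect of 0.5 SD at t3; the same SD at both visits; normal data.

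**The plan's own figure.** The only related figure is the sample size, "for a sample size of 45 cases in each group", for 64.5% against 80% with "two-tailed tests of a significance level of α = 0.05 and β = 0.1". It does not reproduce:

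n = [1.96·√(2·0.7225·0.2775) + 1.2816·√(0.645·0.355 + 0.8·0.2)]² / 0.155² = (1.2412 + 0.7993)² / 0.024025 ≈ 173.3, so 174 per arm.

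That is a separate matter. Here 45 serves only as the number of evaluable patients per arm.

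**Step 1: what the rule becomes with two time points.** With one baseline and one post-treatment value, the group-by-time test of a repeated ANOVA is the t-test on change. If normality is rejected, it is a U-test on change.

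**Step 2: variances in units of SD².**

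- Change score: 2(1 − ρ)
- ANCOVA: 1 − ρ²
- Ratio, ANCOVA to change: (1 − ρ²) / [2(1 − ρ)] = (1 + ρ)/2

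**Step 3: power.** With variance V and n = 45 per arm, power ≈ Φ(0.5/√(2V/45) − 1.96).

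| ρ | V change | V ANCOVA | Ratio | Power, change | Power, ANCOVA |
|---|---|---|---|---|---|
| 0.3 | 1.40 | 0.91 | 0.65 | 52% | 70% |
| 0.5 | 1.00 | 0.75 | 0.75 | 66% | 78% |
| 0.7 | 0.60 | 0.51 | 0.85 | 87% | 91% |
| 0.8 | 0.40 | 0.36 | 0.90 | 96% | 98% |

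Example at ρ = 0.5: √(2/45) = 0.2108. For change, 0.5/0.2108 − 1.96 = 0.41, so 66%. For ANCOVA, 0.5/(0.2108·√0.75) − 1.96 = 0.78, so 78%.

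**Step 4: simulation check.** 4,000 runs per ρ, normal data, 45 per arm, with the effect reset at each ρ to give the change score about 80% power.

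| ρ | t-test on change | Mann–Whitney on change | ANCOVA |
|---|---|---|---|
| 0.5 | 79% | 78% | 89% |
| 0.7 | 79% | 77% | 84% |
| 0.8 | 79% | 77% | 83% |
| 0.9 | 79% | 77% | 80% |

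The loss against ANCOVA is about 10 points at ρ = 0.5 and nearly gone at 0.9. Mann–Whitney costs 1 to 2 points more.

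**The case against.** The strongest reply is that the section already contains what is being asked for. A mixed model is planned for repeated outcomes in secondary analyses. The adjusted regressions of change would give exactly the ANCOVA treatment estimate if baseline were among the covariates, because subtracting baseline from the response alters only the baseline coefficient. A condensed article may leave the covariate list to the full protocol or SAP. The rule also names no outcome, so applying it to H-max/M-max is an inference.

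Much of this stands. A reader might infer that unadjusted change is the only planned secondary analysis, and the article does not support that. What remains is that the article writes out baseline adjustment for MAS alone, states an unadjusted rule in full, adds the other models beside it and ranks none. For H-max/M-max a mixed model does not settle the matter. With one post-baseline value it becomes ANCOVA if baseline is a covariate, or the change-score test if baseline is an unconstrained response, and the article does not say which.

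Other stronger readings also fail:

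- **That baseline is thrown away.** It is subtracted; the loss comes from fixing the slope.
- **That much of the power is always lost.** This depends on ρ and is small at 0.8 or above.
- **That the four-visit outcomes lose some 30 points.** A figure near 95% for a baseline-adjusted analysis needs the mean of t1–t3 and an effect constant from the first session. For the t3 contrast at ρ = 0.5 a check gave about 76%, against about 68% for the group-by-time test.
- **That skewed data will mostly trigger Mann–Whitney.** The article gives no distributional information.
- **That H-max/M-max is the only nerve measure.** MCV is another, used for safety.

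**Conclusion.** The point holds as a moderate, inexpensive improvement to the secondary analyses. It is not an error of validity: the change-score tests keep their type I error near 5%, and the MAS model is unaffected.

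For H-max/M-max and MCV, the stated rule is less precise than ANCOVA for any ρ below 1. At an assumed 0.5 SD effect with 45 per arm, the cost is about 12 points of power at ρ = 0.5, 4 to 5 at 0.7 and 2 at 0.8. The (1 + ρ)/2 ratio rests only on equal variances at the two visits. The power figures rest also on the assumed ρ and effect size and on normal data. That the rule governs these outcomes is the natural reading, not an explicit statement. If it was meant for MAS too, it would compete with the primary model, which would also need to be resolved.

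**What to change.** Name one baseline-adjusted model as the main analysis of each secondary outcome:

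- **H-max/M-max and the MCV parameters:** ANCOVA of the t3 value on arm and that outcome's own baseline.
- **RMS, iEMG, CR, MyotonPRO and IRT:** the mixed model already planned, fitted to t1–t3 with arm, visit, arm-by-visit and the outcome's own baseline, and with the t3 contrast reported.

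Drop the normality-based switch and keep the rank test as a sensitivity analysis. State that the other regressions are supportive. A log transform for measures expected to be skewed is optional; if wanted, fix it before unblinding.

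The cost is a few sentences in the analysis section. The baseline values are already collected, so no new data, visits or patients are needed.

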### Inclusion Criteria

Participants will be qualified for inclusion when they meet the following criteria: (1) meeting the “criteria for the diagnosis of cerebrovascular diseases” adopted by the Fourth Academic Conference on Cerebrovascular Diseases in 1995 (43) and confirmed using computed tomography or magnetic resonance imaging examination of the head; (2) age between 35 and 75 years old, with a first episode > 1 month and being in a stable clinical condition; (3) the presence of hemiplegic or hemiparesis with elbow joint spasticity grade > 1, determined by MAS (31); (4) no obvious cognitive impairment; and (5) the informed consent form being completed by the patient.

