### Outcome Measures

#### Primary Outcome Measure: Modified Ashworth Scale

The scale is graded in six stages, ranging from 0 (no increase in tone) to 4 (limb rigid in flexion or extension). For the convenience of statistical analysis, a MAS grade of 1+ is to be substituted with a value of 2, whereas grades 2, 3, and 4 are to be substituted with values of 3, 4, and 5, respectively Table 1.

**Table 1 T1:** Definitions of MAS for grading muscle spasticity.

**Grade**	**Modified ashworth scale (28)**	**Values**
0	No increase in muscle tone;	0
1	Slight increase in muscle tone, manifested by a catch and release or by minimal resistance at the end of the range of motion when the affected part is moved in flexion or extension;	1
1+	Slight increase in muscle tone, manifested by a catch, followed by minimal resistance throughout the remaining (less than half) range of motion;	2
2	More marked increase in muscle tone through most of the range of motion, but affected part easily moved;	3
3	Considerable increase in muscle tone, passive movement difficult;	4
4	Affected part(s) rigid in flexion or extension.	5

*For convenience of statistical analysis, a Modified Ashworth Scale grade 1+ is to be substituted with a value of 2, and grade 2, 3 and 4 are matched to 3, 4, and 5, respectively*.

(1) Recovery: Muscle tension had completely returned to normal;(2) Obvious effect: The muscle tension had not returned to normal, but muscle tension had decreased by two levels;(3) Effective: Muscle tension had decreased by 1 level;(4) Inefficacy: No change in muscle tone pre- and posttreatment.

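### A second rule, chosen by a normality check, overlaps the baseline-adjusted mixed model for MAS without being limited to other outcomes, and the model's last step appears to omit baseline

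*Protocol article*

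**What the plan says.** All the analysis text is in the protocol article under Statistical Methods.

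- First paragraph, the MAS model: "The primary comparisons for MAS will be made using repeated measures mixed-effect model with terms of treatment, time, and corresponding baseline values as covariates". The order of testing follows: "We will first examine the intervention by time interaction and then proceed to the main effects model with only group and time".
- Second paragraph, a further between-arm rule: repeated ANOVA with post-hoc tests "to compare changes between active rESWT intervention and sham rESWT intervention groups from baseline to the end of follow-up when data are normally distributed", and Mann-Whitney when they are not. Chi-square is added for dichotomous variables. No outcome is named.
- Third paragraph, introduced as secondary analyses: the mixed model is used there too, with linear or logistic regression in addition.
- Last paragraph: intention-to-treat, multiple imputation by chained equations, and significance at p < 0.05.

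On the outcome itself, the primary outcome section says "The scale is graded in six stages, ranging from 0 (no increase in tone) to 4", recoded to the integers 0-5, and then defines four response categories (recovery, obvious effect, effective, inefficacy). Inclusion criterion 3 requires "the presence of hemiplegic or hemiparesis with elbow joint spasticity grade > 1, determined by MAS", so entry scores are 2 to 5. The Sample Size Calculation rests on effectiveness rates of 64.5% and 80%.

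**The concern.** The second paragraph covers the same kind of quantity as the first: the difference between arms in change up to the last visit. Because it stands before the secondary analyses and excludes nothing, it can be applied to MAS. The results could then include two between-arm p-values for the primary outcome, from analyses that handle baseline and the intermediate visits differently, with no rule for a disagreement.

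Choosing between tests by a normality check on the outcome data is weak practice for any variable. For MAS it is worse, because the result of the check depends mainly on which normality test is used, and the protocol names none.

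At stake are a type I error above 5% if either analysis can be presented as the main result, and a loss of power if the rule moves the analysis away from the stated model. The primary model also has a loose end: a final model with group and time only may be fitted without the baseline term listed one sentence earlier.

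**Working it through.** **1. The two rules side by side**

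| | First paragraph | Second paragraph |
|---|---|---|
| Outcome | MAS, called primary | none named |
| Method | repeated-measures mixed model | repeated ANOVA if normal, Mann-Whitney if not |
| Baseline | covariate, then apparently absent from the last step | enters through the change score |
| Visits | t1, t2, t3 | Mann-Whitney on change: baseline and last visit |
| Precedence | none stated | none stated |

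The third paragraph already gives the repeated secondary outcomes a mixed model. If the second paragraph is meant only for those, they have two methods instead.

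**2. Where the normality check sends MAS**

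Entry scores are 2-5 and follow-up scores 0-5, so change (follow-up minus baseline) lies between 0 - 5 = -5 and 5 - 2 = +3, in whole steps. Six-level scores were simulated by rounding a normal variable (SD 0.8 to 1.4, assumed):

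- Shapiro-Wilk rejected normality in 100% of samples at n = 45 to 100, and Lilliefors in 99-100%.
- Three- and four-level change or baseline scores: Shapiro-Wilk rejected in 100%.
- The D'Agostino skewness-kurtosis test rejected in only about 3-8% at n = 45-50, and in up to 24% at n = 100.

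The same data therefore go to Mann-Whitney under one common test and usually to repeated ANOVA under another.

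**3. Type I error if more than one test may count**

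The upper bound is 2 × 5% = 10% for two tests and 3 × 5% = 15% for three. The tests are correlated, so the actual rates are lower. The protocol gives no MAS distribution, so all are assumed:

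| Setting, no true effect | Tests that may count | Rate |
|---|---|---|
| 50 per arm, one follow-up visit | baseline-adjusted ANCOVA or Mann-Whitney on change | 6.4% |
| 45 per arm, all visits | baseline-adjusted analysis or Mann-Whitney on change | 8-9% |
| 50 per arm, one follow-up visit | ANCOVA, t-test on change, Mann-Whitney or responder chi-square | 9.1% |
| 45 per arm, correlation 0.7 | mixed model, Mann-Whitney on last-visit scores or responder chi-square | 10.1% |

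In the 50-per-arm runs each test alone held 5.0-5.2%. With a true shift of 0.35 points, ANCOVA and Mann-Whitney gave different verdicts in about 9% of trials.

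**4. Efficiency**

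Take equal variance σ² at every visit and correlation ρ between any two visits. The variance of the arm difference is 2σ²/n times:

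- change to the last visit: 2(1 - ρ)
- last visit adjusted for baseline: 1 - ρ²
- mean of three visits adjusted for baseline: (1 + 2ρ)/3 - ρ²

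With ρ = 0.7 (assumed) these are 0.60, 0.51 and 0.80 - 0.49 = 0.31. With σ = 1 and n = 45 the standard errors are √(2 × 0.60/45) = 0.163, √(2 × 0.51/45) = 0.151 and √(2 × 0.31/45) = 0.117. For a 0.4-point effect at every visit, power = Φ(0.4/SE - 1.96), which gives about 69%, 76% and 93%.

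This is a normal approximation without rounding of scores. Simulation with rounded scores (45 per arm, several assumed distributions) gave 43-69% for Mann-Whitney on change and 79-96% for the baseline-adjusted analysis of all visits.

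One condition matters. If the effect builds up in thirds (0.133, 0.267, 0.4), its mean over visits is 0.267, and the averaged main effect has power Φ(0.267/0.117 - 1.96), about 62%, below the 69% for change. The last-visit contrast adjusted for baseline keeps its advantage over change (0.51 against 0.60) in either case.

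**The case against.** The strongest reply is that the primary test is named. Only the mixed model is called primary and only it is tied to MAS. The second paragraph can be read as generic rules for the electromyographic, conduction, MyotonPRO and thermal outcomes, and its chi-square as meant for adverse events. A reader might infer that the MAS analysis is fixed twice and that the deciding test is open; the text does not support that, because the primary label is explicit. What stands is narrower: the second paragraph is not limited to other outcomes, no precedence is stated, and the label must carry the whole distinction.

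Four other strong readings also fail:

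- That MAS must always fail a normality check. It does under Shapiro-Wilk or Lilliefors at this sample size, but usually not under a skewness-kurtosis test.
- That Mann-Whitney would disregard baseline. The rule concerns changes, which contain baseline; what it lacks is covariate adjustment and the intermediate visits.
- That repeated ANOVA would discard patients with a missed visit, against intention-to-treat. Multiple imputation is planned.
- That chi-square is a planned MAS test. The protocol defines four response categories and does not assign chi-square to MAS. It matters only because the sample size is built on an effectiveness rate, which makes a responder comparison a plausible rival.

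The wording about group and time only may simply mean without the interaction. That is a fair reading, but it should be written down.

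A fuller protocol or SAP may set out the hierarchy. The overlap criticised here is nevertheless in the published text.

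**Conclusion.** The concern holds in a limited form. The protocol names a baseline-adjusted mixed model as primary for MAS, then gives an overlapping, data-dependent rule that does not exclude MAS, and describes the model's last step in a way that appears to omit baseline.

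If either the model or Mann-Whitney could be taken as the result, type I error is about 6-9% against a nominal 5%, or about 9-10% with a responder chi-square as well. These rates apply only if the primary label is disregarded. If the label is kept and baseline stays in the model, there is no inflation from this source.

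Mann-Whitney on change is less efficient than the stated model: 43-69% against 79-96% power at 0.4 points. The size of that gap depends on an effect that is similar at all three visits. With an effect that builds up, the averaged main effect can lose its advantage, while baseline adjustment at the last visit remains better than change. All these figures rest on assumed MAS distributions and between-visit correlations and are illustrative. The contradiction in wording does not depend on them.

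**What to change.** Amend Statistical Methods as follows:

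1. State that the only confirmatory MAS analysis is the repeated-measures mixed model with baseline as covariate, and that baseline stays in at every step, including the model with group and time. Say in the same sentence which term or contrast decides, since the averaged effect and the last-visit contrast can differ.
2. Remove the normality-dependent choice between repeated ANOVA and Mann-Whitney for MAS.
3. Label any rank-based, ordinal or responder analysis of MAS as a sensitivity analysis that cannot replace the primary result.
4. Analyse the continuous secondary outcomes with the same baseline-adjusted mixed model instead of a test picked by a normality check.

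The cost is a few sentences and approval of the amendment by the ethics committee, as the protocol requires for any modification. No new data or patients are needed. At submission 50 of 100 patients had been recruited, and unblinding is planned only after the statistical judgment is complete, so the change should be made and dated before unblinding.
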